##### Timed up and go test

To measure patients’ functional mobility, timed up and go (TUG) test will be used. The TUG test is a validated and effective tool to assess the participants functional mobility and the gait related motor symptoms common in PD (da Silva et al., 2017). The TUG involves sequential motor tasks that incorporate arising from a chair, walking, and turning around all of which are affected by PD. All assessors are trained in the administration of the TUG.

##### Montreal cognitive assessment

Cognitive impairment is a significant non-motor symptom of PD with as many as 80% of patients exhibiting decline in function (Flores-Torres et al., 2021). A frequently used assessment tool is the Montreal Cognitive Assessment (MoCA) a brief tool that assesses several cognitive domains. The MoCA is validated for use in 55–85-year-olds and recommended as a scale for cognitive screening in PD (Chou et al., 2010; Fang et al., 2020). The assessment consists of a 30-point test on a single side of A4 paper and can be administered in 10 min. All assessors are trained in the administration of the MoCA.

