## Methods and analysis

### Trial design

The study is a 24-week, two-arm, triple blinded randomized placebo-controlled trial evaluating the safety and effectiveness of the “PDNeuro” Helmet (see Figures 1, 2) compared with a sham helmet device. Treatment will consist of PBMt to the head six times per week for 12 weeks (see Figure 3), with Group 1 (the active group) receiving 12 min of infra-red and 12 min red LED, and Group 2 (the sham group) receiving sham treatment for 24 min. After the initial 12 weeks, the sham patients will be given the active treatment for 12 weeks while the active treatment group will have a 12 weeks washout period and then be re-assessed in 12 weeks (see Figure 3). Outcome measures will be collected by the study investigators that have received specialized training in assessment and data collection.

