### Randomization

Following virtual screening and informed consent, 40 participants will be randomized into two groups and then allocated into a treatment or sham group *via* an independent research administrator and thereafter identified *via* an anonymous SN (serial number). To reduce the chance of participants inadvertently realizing that they are in the sham group, the HREC approved that the participants be informed there are four groups: active infrared, inactive infrared, active red + infrared, inactive red + infrared. Group 1 will receive active treatment and Group 2 will receive a sham helmet, which is identical in appearance. Participants will be instructed on helmet use by a trained technician *via* Zoom video communication.

By intention there will be equal numbers of males and females in each group. While it is well-known that gender differences effect human disease including PD, little research has been performed into the different gender responses to PBMt (Liebert et al., 2022). Therefore, the efficacy and tolerability outcomes of PBMt transcranial delivery will be subject to sub analysis based on gender.

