### Outcome measures

Due to the broad clinical signs and symptoms of PD, a range of outcome measures were selected to determine functional improvement (Table 1). Many PD clinical rating scales have been developed since the 1960s that assess both motor and non-motor functions (Ramaker et al., 2002) and all outcome measures to be used in this study have been validated for use in PD remotely (Abdolahi et al., 2013; Stillerova et al., 2016). The primary outcome measures will be conducted and recorded using a combination of self-reported assessment and visual assessment obtained *via* Zoom video link. Outcome measures will be supervised, and data will be collected *via* specialist examiners and physiotherapists all trained in conducting each assessment. Outcome measures will be obtained at baseline, 12-week and 24-week intervals (see Figure 3).

**TABLE 1 T1:** Outcome measurements.

Primary outcome measurements	Data collection tools
1. Safety of PDNeuro helmet device	24-h access to health personnel Weekly [or as needed] technical meetings
2. Motor assessment	MDS-UPDRS [Modified Part 3 Motor component]
3. Social experiences and difficulties	PDQ39

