#### Secondary outcome measurements

1.Movement mobility (TUG [non-cognitive])2.Cognition (MoCA)3.Writing task (assess writing size)4.Sleep habits self-assessment (PDSS sleep scale)5.Carer’s diary of daily living

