### Statistical analysis

This is a feasibility study trialing the efficacy of the “PDNeuro” Helmet transcranial device. The sample size of 40 participants falls within the recommendation of between 12 and 50 for feasibility clinical studies (Julious, 2005; Sim and Lewis, 2012). As a series of *N* = 1 studies, it is anticipated that only basic statistical analysis will be performed. For each outcome measure, descriptive data (mean, standard deviation) will be calculated. From this data, “minimally important difference” (MID) scores will be computed based on 1/2 SD of each measure. This is a common MID measure (Norman et al., 2003) based on the distribution of the participant scores at baseline and provides a sensitive indicator of significant change over time for *N* = 1 case studies. This has also been used with good effect in previous PBMt PD trials (Liebert et al., 2021). As such, it does not suffer from a lack of statistical power that would be evident with more traditional ANOVA approaches with small sample sizes. The number of participants showing improvement (i.e., difference between two time points > MID) can be compared between time points with chi-square analyses.

In total, 162 participants (81 + 81) were proposed for recruitment over a 2-year period. However, due to limitations involving in no small part to the substantial COVID-19 restrictions during the conception of this trial, the decision was made to reduce the total number of participants to 40, with the intention of increasing this by 122 at a later date.

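### The only stated test compares improver counts between time points, so on the repeated MoCA any practice gain can mimic or mask a device effect, and the randomised sham contrast goes unused

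*Protocol article*

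**What the plan says.** Under Outcome measures, the protocol article states: "Outcome measures will be obtained at baseline, 12-week and 24-week intervals". The MoCA is a secondary outcome and is therefore taken three times. The section on it says: "The assessment consists of a 30-point test on a single side of A4 paper and can be administered in 10 min". That sentence describes the instrument and is not itself wrong.

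The fault lies under Statistical analysis. Minimally important difference (MID) "scores will be computed based on 1/2 SD of each measure", taken from the baseline distribution. A participant counts as improved if the change between two time points exceeds that threshold, and the number improved "can be compared between time points with chi-square analyses". The section does not fix which two time points are meant, and it names no comparison of the active arm with the sham arm.

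Under Randomization, "40 participants will be randomized into two groups". Under Trial design, "the sham patients will be given the active treatment for 12 weeks while the active treatment group will have a 12 weeks washout period". Group 1 therefore always runs active then washout, and Group 2 always runs sham then active.

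**The concern.** A performance test can improve on repetition through familiarity. At week 12 both randomised arms have sat the MoCA twice, so a practice gain is common to them and drops out of the difference between arms. A comparison between time points has no such protection, because the later occasion always carries more exposure to the test. With the order fixed in each group, test occasion and treatment period change together and the counts cannot tell them apart.

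The trial is a feasibility study, but efficacy is among its stated objectives, the secondary hypothesis covers non-motor symptoms, and the results are meant to inform a larger trial. A cognitive signal created or hidden by repeat testing would carry forward into that design.

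**Working it through.** **No plan figure to reproduce.** The article gives no power, alpha or effect size for this test.

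**Inputs from the protocol article.** Three assessments (Outcome measures); threshold of half the baseline SD and a chi-square between time points (Statistical analysis); fixed order in each group (Trial design); 40 participants in two groups (Randomization).

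**Assumed, because the documents give no values.** 20 per group; MoCA mean 25 and SD 3 points; test-retest correlation r from 0.7 to 0.9; practice gain 0 to 2 points; no device effect; uncorrected chi-square at two-sided 5%.

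**Step 1: where practice enters.** Let p1 be the mean practice gain from test 1 to test 2, p2 the gain from test 2 to test 3, and d the device effect. Leave aside placebo response and any loss of effect in washout. In mean change:

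- Group 1, active interval minus washout interval: (d + p1) - p2 = d + p1 - p2
- Group 2, active interval minus sham interval: (d + p2) - p1 = d + p2 - p1
- Group 2, change from baseline at week 24 minus that at week 12: (p1 + p2 + d) - p1 = d + p2
- Active minus sham at week 12: (d + p1) - p1 = d

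Only the last is free of practice. The first two carry biases of opposite sign.

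**Step 2: share classed as improved by week 12 with an inert device.** With g the gain in SD units, P(improved) = 1 - Phi((0.5 - g) / sqrt(2(1 - r))).

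- No gain: r = 0.7 gives 1 - Phi(0.5/0.775) = 26%; r = 0.9 gives 1 - Phi(0.5/0.447) = 13%.
- 1 point (g = 1/3): 1 - Phi(0.167/0.775) = 42% (41.5%) to 1 - Phi(0.167/0.447) = 36% (35.5%).
- 2 points (g = 2/3): 58% (r = 0.7) to 65% (r = 0.9, 64.5%).

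**Step 3: the stated test, simulated.** 20,000 trials per setting, integer scores, no ceiling, inert device. Ranges are over r = 0.7 to 0.9. The first three result columns count significant results in the named direction, for which the nominal rate is 5%/2 = 2.5%. The last is two-sided, nominal 5%.

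| Gain at test 2, then test 3 (points) | Group 1 intervals, favours active | Group 2 intervals, favours sham | Group 2 from baseline, favours later (active) | Active vs sham, week 12 |
|---|---|---|---|---|
| 0, 0 | 3-4% | 3-4% | 1% | 4.6-5.4% |
| 1, 0 | 22-39% | 21-38% | 1% | 4.8-5.2% |
| 1, 0.5 | 10-17% | 11-17% | 4-9% | 4.5-5.1% |
| 1, 1 | 4-5% | 4-5% | 13-39% | 4.6-5.2% |
| 2, 0 | 53-91% | 53-91% | 1% | 4.6-5.0% |

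With gains of 1 then 0, Group 2's interval contrast favours active in at most 0.5% of trials. The size and the direction of the error both depend on which pair of time points is chosen and on when practice accrues.

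**Step 4: a milder case.** With gains of 0.5 point in each interval, a ceiling at 30 and r of 0.75-0.9, Group 2 improvers measured from baseline go from 22-31% at week 12 to 34-39% at week 24. The chi-square favours the active period in 4-8% of trials measured from baseline, and in 3-4% measured by interval.

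**The case against.** The strongest objections are these.

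- **The practice gain is assumed.** True. The documents give no gain, SD or retest correlation, and with modest gains (step 4) the planned test rarely misleads. This limits the claimed size. It does not restore the test's ability to separate practice from treatment.
- **A reader might infer that one MoCA form is reused.** The article does not say so. The single-sheet description gives the test's length, and the choice of form at each visit may sit in the full protocol. No fault is shown there.
- **A reader might infer that practice always inflates the device effect, most of all in Group 2's move from sham to active.** Steps 1 and 3 do not support this. In Group 2's interval contrast an early gain falls in the sham period and works against the device. Nor is that contrast what the design is built to show: Advantages and limitations speaks of differences between the treatment and sham groups.
- **The point is general and the MoCA is one of five secondary outcomes.** Largely right. The root fault is that the stated test does not use the randomised contrast, and the TUG is exposed in the same way. The MoCA is a clear instance, not the only one.
- **A separate analysis plan may name the arm comparison.** Possible. But the article does more than stay silent: it promises only basic analysis, names this test and presents the approach as avoiding the low power of ANOVA-type methods.

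**Conclusion.** The point holds in a limited form. Followed as written, the plan's only stated test cannot separate repeat-testing gains from the device on the MoCA, and it leaves unused the sham contrast that would do so. Under the assumptions listed, the rate of spurious significance in a given direction runs from about 1% or less to 91%, depending on the time points compared and on the size and timing of practice. The week-12 active-versus-sham test stays at 4.5-5.4% throughout. The confounding follows from the article alone; the percentages rest on the assumed SD, correlation, gains and group size. Because the MoCA is secondary in a feasibility study, this is a correction that should be made and not a threat to the trial as a whole.

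**What to change.** In Statistical analysis, state that the MoCA, and likewise other repeated performance measures such as the TUG, will be judged on the active-versus-sham difference in week-12 score adjusted for baseline score, with its confidence interval. State also that improver counts between time points, including Group 2's change from week 12 to 24 and Group 1's washout change, are descriptive only and include any practice effect.

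The week-12 false-positive rates above are for a chi-square of improvers between arms. The adjusted difference is protected for the same reason: with an inert device, both arms have the same distribution of scores whatever the practice gain.

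The cost is a few sentences, with no added participants, visits or data. What is given up is any formal efficacy claim from the second 12 weeks on these measures. Alternate MoCA forms, balanced across arms, are an optional refinement, and the fix does not depend on them.

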##### Writing task

Micrographia is a common clinical feature associated with PD and a measure of PD progression (Smits et al., 2014; Hamilton et al., 2019). Participants will be asked to write “the quick brown fox jumps over the lazy dog” and sign their name ten times and note of potential change in size will be recorded over the same three time-points.

##### Carer’s diary

A carer’s diary can provide qualitative data on patient experiences, as well as note changes in clinical manifestations that are not observed in the clinical environment. This information in the areas of physical, cognitive, and emotional domains can reveal both positive and negative changes and may provide a more detailed picture of the effect of treatment.

### Safety considerations

Photobiomodulation is considered a safe treatment. In over 50 years of research on the effects of PBMt, there have been limited published results of harm when used within the correct dose window. Cassano et al. (2019) noted transitory and benign side effects of transcranial PBMt and Maiello et al. (2019) reported one case of severe headache, which led to discontinuation of treatment.

Dosing protocols for the PD trial have been based on both clinical experience by members of the research team and others (Dompe et al., 2020). To provide for patient safety, a suspected adverse event committee was formed consisting of the coordinating chief investigator, a neurologist from the research team, and an independent neurologist. A member of this team will be available *via* phone 24/7 to address any concerns that arise.

Safety will be assessed at weekly intervals in pre-organized Zoom meetings and at any other time as required. All suspected adverse events (SAE) will be followed up with the Committee coordinating chief investigator and all relevant medical history documented and maintained in a file of “identified” subjects.

All device issues will be directed to the device support officer. In the case of helmet failure, the faulty device will be repaired by a qualified medical devices electrical engineer, or a new device will be provided.

### Patient timeline

The schedule of clinical research activities is illustrated in Table 2. Participant investigator interaction will consist of four Zoom meetings for screening and assessment and Zoom meetings weekly for initial and ongoing device management. As well, ongoing email, telephone calls, and Zoom meetings will be provided as necessary during the period of device usage.

**TABLE 2 T2:** Patient timeline.

Week 1: Email received at Trial office
Week 1: Zoom meeting organized for initial screening and consent
Week 2: Zoom meeting to obtain baseline assessments
Week 3: Zoom meeting for device management and treatment with PDNeuro Helmet
Week 3: Treatment commences
Weekly: Email, telephone, and Zoom meetings for ongoing device concerns as required
Week 12: Zoom meeting re-assessments
Week 12: Email and telephone call to organize return of PDNeuro Helmet
Week 12: Patients from sham group provided with active PDNeuro Helmet
Weekly: Email, telephone, and Zoom meetings for ongoing device concerns as required to second treatment group
Week 24: Zoom 6-month follow-up of all baseline assessments

### Data collection

Once accepted on the trial all data will be stored in a secure location both in paper and electronic form. Data collected will include patient’s sociodemographic data and clinical history. Next, the primary outcomes and the secondary outcomes of the study will be collected. At the end of 12 weeks, the primary and secondary outcomes of the study participants will be reassessed by the same evaluator who performed the baseline assessment. Further data will be collected following 24 weeks when Group 2 (the sham group) have also had the chance to experience the treatment and Group 1 (the initial treatment group) have had a 12-week washout. The investigators responsible for collecting all outcome measurements will be blinded to the treatment being administered to the patients.

### Statistical analysis

This is a feasibility study trialing the efficacy of the “PDNeuro” Helmet transcranial device. The sample size of 40 participants falls within the recommendation of between 12 and 50 for feasibility clinical studies (Julious, 2005; Sim and Lewis, 2012). As a series of *N* = 1 studies, it is anticipated that only basic statistical analysis will be performed. For each outcome measure, descriptive data (mean, standard deviation) will be calculated. From this data, “minimally important difference” (MID) scores will be computed based on 1/2 SD of each measure. This is a common MID measure (Norman et al., 2003) based on the distribution of the participant scores at baseline and provides a sensitive indicator of significant change over time for *N* = 1 case studies. This has also been used with good effect in previous PBMt PD trials (Liebert et al., 2021). As such, it does not suffer from a lack of statistical power that would be evident with more traditional ANOVA approaches with small sample sizes. The number of participants showing improvement (i.e., difference between two time points > MID) can be compared between time points with chi-square analyses.

In total, 162 participants (81 + 81) were proposed for recruitment over a 2-year period. However, due to limitations involving in no small part to the substantial COVID-19 restrictions during the conception of this trial, the decision was made to reduce the total number of participants to 40, with the intention of increasing this by 122 at a later date.

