### Advantages and limitations

This is a triple blinded RCT designed to minimize bias and maximize the validity of any differences observed between the treatment and sham groups. While the triple blinding of this RCT is an advantage, restrictions resulting from SARS-CoV-2 affected the initial protocol, creating several limitations. Due to restrictions in Australia during the conception of this trial, it was not feasible to invite participants into a clinic setting for in-person intervention and assessments due to government regulations at the time. Furthermore, the increasing rate of infections and hospitalizations during this period meant that movement of research staff and participants to and from a clinic/hospital location would introduce an increased risk of potential COVID-19 infection. Therefore, the decision was made to pivot the study to a home-based trial to minimize as much person-to-person contact as possible, and to mitigate any risk of infection to our vulnerable population.

The scientific/clinical validity and feasibility of conducting our RCT remotely had been assessed prior to commencement of the study. For example, the UPDRS assessment used for the RCT has been shown to be clinically valid when conducted remotely (Schneider et al., 2020). Indeed, the feasibility, reliability, and value of implementing remote telemedicine/video-based assessments for Parkinson’s disease patients for both research (Tarolli et al., 2020) and ongoing healthcare (Cubo et al., 2020) have been previously evaluated and deemed valid. Furthermore, all outcome measures will be assessed by medical professionals (physicians, nurses, physiotherapists) who have been trained to conduct clinical assessments in Parkinson’s disease patients, with supervision of leading neurologist to ensure assessment accuracy and reliability.

The resulting limitation is that treatment is delivered unsupervised with only a carer present. This means that there is a reliance of self-reporting and participant honesty that the “PDNeuro” Helmet is being applied correctly for the duration of the treatment period. Assessments are also being recorded *via* video communication and although cameras are effective in providing visual feedback it is possible that fine tremors may be missed and reliance of carers to manipulate the camera and give good visual observation may present a challenge.

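### Half a baseline SD is presented as an indicator of significant change in a single participant, but it says nothing about retest error, and counting improvers between time points does not remove those produced by noise

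*Protocol article*

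**What the plan says.** The Statistical analysis section of the protocol article treats the trial as a series of N = 1 studies, for which "it is anticipated that only basic statistical analysis will be performed". Minimally important difference (MID) "scores will be computed based on 1/2 SD of each measure". The SD meant is the spread between people before treatment, since the measure is described as "based on the distribution of the participant scores at baseline". The section then says that this threshold "provides a sensitive indicator of significant change over time for" N = 1 case studies.

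A participant counts as improved when there is a "difference between two time points > MID". The numbers improved "can be compared between time points with chi-square analyses". The section also says of the approach that "it does not suffer from a lack of statistical power that would be evident with more traditional ANOVA approaches with small sample sizes".

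According to Outcome measures, assessments take place at baseline, week 12 and week 24, so there is one pre-treatment assessment per person. No test-retest reliability, measurement error or false-positive rate is given for any scale.

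**The concern.** The between-person SD describes how much participants differ from one another. Whether one participant's change is more than noise depends on how much the same person's score varies between two occasions when nothing has changed. A threshold built from the first quantity can be a convention for how large a change matters. It cannot show that a change in one person is real unless reliability is also known.

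If ordinary retest variation often exceeds half a baseline SD, some participants will be labelled improved on each scale even if the device does nothing. A sham comparison would carry the same noise rate and so subtract it. The comparison the section names is between time points, which does not. The abstract makes sustained symptom improvement the main indicator of efficacy, and Dissemination of results says the findings are to inform patient management and a larger trial. An inflated count of improvers would therefore be used.

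**Working it through.** The plan states no error rate or power for the rule, so there is no figure of its own to reproduce. The check asks how often the rule labels an unchanged participant as improved.

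**Inputs**
- Threshold: 0.5 baseline SD (Statistical analysis).
- Rule: one difference between two single assessments, in the direction of improvement (same section).
- Participants per arm: 40 / 2 = 20, assuming equal allocation.
- Test-retest reliability r: not given, so assumed to lie between 0.70 and 0.95. The UPDRS section calls internal consistency and inter-rater reliability high, but neither is retest stability over 12 weeks.
- Normal errors and no true change, placebo, practice or progression effect (assumed).

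**Formulas**, in units of the baseline SD
- SD of change in an unchanged person: s = sqrt(2(1 − r)).
- Probability of being labelled improved: P = 1 − Φ(0.5 / s).
- Change needed for a one-sided 5% individual rule: 1.645 × s.

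At r = 0.80, for example, s = sqrt(0.40) = 0.632, P = 1 − Φ(0.791) = 21.5%, and the one-sided threshold is 1.645 × 0.632 = 1.04 SD.

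| Assumed r | s | P (labelled improved) | Expected of 20 | One-sided 5% threshold |
|---|---|---|---|---|
| 0.70 | 0.775 | 25.9% | 5.2 | 1.27 SD |
| 0.80 | 0.632 | 21.5% | 4.3 | 1.04 SD |
| 0.90 | 0.447 | 13.2% | 2.6 | 0.74 SD |
| 0.95 | 0.316 | 5.7% | 1.1 | 0.52 SD |

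**Simulation.** With the SD estimated from 40 baseline scores, as the plan would have to do, the rates are 26.2%, 21.7%, 13.5% and 6.1%, so estimating the SD changes little.

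**Break-even reliability.** Half an SD meets the one-sided 5% rule only when r is at least 1 − (0.5/1.645)² / 2 = 0.954. For a two-sided 95% band it is 1 − (0.5/1.96)² / 2 = 0.967.

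**Side check on the power claim.** Suppose a true shift of 0.5 SD, 20 per arm and a two-sided 5% test. In the active arm the chance of exceeding the threshold is then 1 − Φ(0) = 50%, and in sham it is P. Comparing these proportions between arms has power 34%, 47% and 72% at r = 0.70, 0.80 and 0.90. Comparing mean changes has 53%, 71% and 94%. Counting improvers does not escape the small-sample problem.

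**The case against.** **Half an SD is a recognised MID, and significant may mean clinically meaningful.** This stands in part. As a convention for importance the threshold is acceptable. The section goes further by tying it to N = 1 and to change over time, and a reader will take that as evidence about an individual.

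**The rates rest on a reliability that the documents do not give.** This stands, and it is why the range runs to 0.95, where the rate is about 6% and the rule is close to a one-sided 5% criterion. The same evaluator scores both visits (Data collection), so a high r for the motor score cannot be excluded. Same-assessor scoring does not, however, remove day-to-day or ON/OFF variation.

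**A sham arm carries the same noise.** True, and Advantages and limitations speaks of differences between the groups. But the only comparison that Statistical analysis names is between time points. A full analysis plan may add an arm comparison; this point concerns the rule as stated.

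**It is a feasibility study with safety as its primary hypothesis.** This limits the weight of the point. The article nevertheless lists motor and quality-of-life scales as primary outcomes and says that efficacy is being tested.

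Two stronger readings are tempting, and the documents support neither:
- A reader might infer that most unchanged participants would improve on at least one scale. The plan defines no any-scale responder, and such a figure would need independent errors across scales. Shared ON/OFF variation in, for example, the motor score and TUG makes that doubtful.
- A reader might infer from the remark that "it is possible that fine tremors may be missed" that video scoring lowers reliability further. A sign missed at both visits by the same assessor shifts the level and need not add noise to the change. The article also regards remote assessment as valid, and PDQ-39 is self-completed.

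**Conclusion.** The point holds as an error of interpretation in a stated rule. Half a between-person SD is not evidence that one person has changed. With r assumed between 0.70 and 0.95, normal errors and no true change, the rule labels about 26% to 6% of unchanged participants as improved per scale, or roughly 5 to 1 of 20. Placebo or practice effects would raise these rates and natural progression would lower them. Only at r of about 0.954 or more does the threshold meet a one-sided 5% standard. Because counts are compared between time points, the false improvers stay in the result. The direction of the error is certain wherever r is below that level; its size cannot be fixed from the documents. The article's description of its outcome, an aggregate count per measure, does not show that named individuals will be reported as responders. The correction is worth making but modest.

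**What to change.** 1. Remove the statement that the threshold indicates significant change for N = 1 studies, and describe 0.5 SD only as a threshold of importance.
2. For each scale, report the proportion improving by more than 0.5 SD in active minus sham at week 12, with a confidence interval. Week 12 is the right time because sham participants then move to the active helmet. Beside it, give the proportions worsening by more than 0.5 SD in each arm, which show how much movement is noise.
3. If individual labels are wanted, use a reliable-change threshold with a reliability for each measure stated in advance. It should not be estimated from the sham arm's own change. An SD from about 20 people (19 degrees of freedom) has 95% limits of roughly 0.76 to 1.46 times the estimate, it mixes real change with error, and the cut-off would not be fixed beforehand.

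The data for items 1 and 2 are already collected, so the cost is wording and an extra table column. Fewer individual responders can be claimed. The interval will also be wide: for proportions of 50% and 21% with 20 per arm, the half-width is 1.96 × sqrt((0.50 × 0.50 + 0.21 × 0.79) / 20) = 0.28, or 28 percentage points. That is a fair picture of what 40 participants can show.

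### The half-SD responder count is justified by a power advantage over ANOVA that it does not have; tested by chi-square, it has less power than an analysis of the same scores

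*Protocol article*

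**What the plan says.** The Statistical analysis section of the protocol article calls the trial a feasibility study and a series of N = 1 studies. The total of 40 is justified by a rule of thumb: "The sample size of 40 participants falls within the recommendation of between 12 and 50 for feasibility clinical studies". It states no effect size, alpha, power, SD or correlation.

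Means and SDs are to be calculated for each outcome. From these, minimally important difference (MID) "scores will be computed based on 1/2 SD of each measure", the SD being "based on the distribution of the participant scores at baseline". The section then claims that "it does not suffer from a lack of statistical power that would be evident with more traditional ANOVA approaches" when samples are small. The next sentence moves to a group test: the number of participants improved ("difference between two time points > MID) can be compared between time points with chi-square analyses").

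Under Randomization, "40 participants will be randomized into two groups". The same section adds, on sex, "By intention there will be equal numbers of males and females in each group", and says that "the efficacy and tolerability outcomes of PBMt transcranial delivery will be subject to sub analysis based on gender".

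**The concern.** The only statistical reason given for preferring the responder count to ANOVA is power, and that reason points the wrong way. A participant who improves by 0.51 SD and one who improves by 2 SD count the same, as do one who improves by 0.49 SD and one who worsens. A test that sees only those two categories cannot in general match one that uses the scores.

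This matters because the MDS-UPDRS motor score and the PDQ-39 are listed as primary outcomes beside safety, the section says efficacy is being trialled, and only 40 of the 162 participants once proposed remain. A trial of this size can least afford to discard information, and a reader who trusts the sentence could take a null chi-square as better evidence of no effect than it is.

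A second difficulty lies in the same sentence as the chi-square. It compares counts between time points, whereas the trial is randomised and sham-controlled. A comparison over time does not use the randomisation, and an ordinary chi-square on the same people at two times also ignores the pairing.

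**Working it through.** **The plan's own figures.** There is no power figure to reproduce. The stated arithmetic is consistent: 40 lies between 12 and 50, 81 + 81 = 162, and 162 − 40 = 122.

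**Inputs from the protocol.** Total 40 in two groups, taken as 20 per arm (implied by equal numbers of each sex in each group and by the earlier 81 + 81); cut at 0.5 baseline SD; chi-square on the counts.

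**Inputs assumed.** Baseline and week-12 scores bivariate normal with SD 1 and correlation ρ; true active-versus-sham difference 0.5 baseline SD; no change under sham; two-sided alpha 0.05.

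**Step 1: information lost, asymptotically.** The change score has variance 2(1 − ρ). The cut in units of its SD is c = 0.5/√(2(1 − ρ)), and the share above it without an effect is p = 1 − Φ(c). The efficiency of the dichotomy relative to the continuous change score is φ(c)²/[p(1 − p)].

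At ρ = 0.7: c = 0.5/0.775 = 0.645, p = 0.259, φ(c) = 0.324, so the efficiency is 0.105/(0.259 × 0.741) = 0.546, a loss of 45%.

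ANCOVA has residual variance 1 − ρ². Since (1 − ρ²)/[2(1 − ρ)] = (1 + ρ)/2, the efficiency against ANCOVA is the figure above times (1 + ρ)/2. At ρ = 0.7 this is 0.546 × 0.85 = 0.464, a loss of 54%.

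| ρ | Loss against change score | Loss against ANCOVA |
|---|---|---|
| 0.3 | 40% | 61% |
| 0.5 | 42% | 56% |
| 0.6 | 43% | 55% |
| 0.7 | 45% | 54% |
| 0.8 | 50% | 55% |

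The smallest possible loss against the change score, with the cut at the median, is 36%.

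**Step 2: the same from sample sizes.** Participants per arm for 80% power, by formula:

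| ρ | Effect (SD) | Responder count | Change score | Loss = 1 − change/responder |
|---|---|---|---|---|
| 0.5 | 0.3 | 288 | 175 | 39% |
| 0.5 | 0.5 | 102 | 63 | 38% |
| 0.7 | 0.3 | 179 | 105 | 41% |
| 0.7 | 0.5 | 63 | 38 | 40% |
| 0.8 | 0.3 | 125 | 70 | 44% |
| 0.8 | 0.5 | 44 | 26 | 41% |

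For effects of realistic size the loss from dichotomising alone is therefore about 38 to 44%.

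**Step 3: power at 20 per arm, effect 0.5 SD.** Simulated trials, cutting at half the observed baseline SD:

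| ρ | Chi-square on responders | Change-score ANOVA | ANCOVA |
|---|---|---|---|
| 0.5 | 23% | 34% | 42% |
| 0.7 | 35% | 51% | 57% |
| 0.8 | 48% | 68% | 72% |

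The order was the same for effects of 0.3 and 0.7 SD, and when both arms were shifted by 0.2 SD to mimic a placebo response. A continuity-corrected chi-square does worse still: 12%, 22% and 34% at these three correlations.

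**Step 4: what is being compared.** Steps 1 to 3 model active versus sham at week 12. The protocol's sentence compares counts between time points. That uses the same dichotomy, so the loss of information carries over in kind, but the percentages are for the between-arm test.

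**The case against.** The strongest defence is that the half-SD rule classifies individuals in N = 1 studies, where group power does not arise, and that a feasibility study with basic analysis need not be powered. The first part fails because the sentence itself claims an advantage over ANOVA, and the chi-square that follows is a group-level test. The second lowers the stakes but does not make the statement correct. It is fair that the chi-square is worded as something that can be done, and that the primary hypothesis concerns safety.

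Several stronger readings are tempting, and the protocol does not support them:

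- A reader might quote one figure, such as 45%, for the information lost. That is the value at an assumed correlation of 0.7. The protocol gives none, and the loss against the change score must be kept apart from the loss against ANCOVA, which also includes the missing baseline adjustment.
- A reader might infer that the data for planning the larger trial would be reduced to proportions. The section promises means and SDs for each outcome.
- A reader might infer that baseline is ignored. The responder rule subtracts it; what the described analysis lacks is adjustment for it as a covariate.
- A reader might infer a chi-square within each sex at 10 versus 10, with expected counts too small for it. The Randomization section announces a sub-analysis but names no test, so no error can be charged there.

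**Conclusion.** The power statement is wrong as written and should be corrected. At every correlation and non-null effect tried, the chi-square on the dichotomised change had less power than ANOVA or ANCOVA on the same scores; in the 0.5 SD example the shortfall against ANCOVA is roughly 19 to 24 percentage points.

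The direction rests on roughly normal scores, and the protocol argues nothing else. The size rests on the assumed correlation, a 0.5 SD effect and 20 per arm. Separately, the comparison as written is between time points and does not test active against sham. No unseen analysis plan could make the power statement true, although such a plan could already contain a better between-arm analysis.

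**What to change.** 1. Delete the sentence claiming that the method escapes the low power of ANOVA.
2. Compare arms at week 12 on each continuous score by ANCOVA with arm, baseline score and sex as terms, and report the adjusted difference with a 95% confidence interval.
3. Keep the half-SD responder proportions, by arm, as description.

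As a suggestion only: if results by sex are reported, an exploratory arm-by-sex interaction with a 95% confidence interval would answer the question more directly than separate results for men and women.

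The cost is wording, since the scores and sex are already to be recorded. The downside is that the responder result is no longer the headline. The change also does not make the trial well powered: ANCOVA reaches only 42 to 72% in the examples above, so the confidence interval should carry the interpretation.
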